### Data management

A secured data platform is designed that contains unique participant IDs, matched with the names and addresses of the participants. A second, secured data platform is designed to enable pseudonymized data transfer and data storage. In this data platform, a computerized record is kept of all home-based screening test results to enable correct dispatching of test results and reminders, and to send confirmation screening tests and invitations for the elaborate screening visit if appropriate. Questionnaires filled out by the participants are sent to the University Medical Center Groningen research team and are recorded digitally in an electronic case report form (eCRF) in a certified Electronic Data Capture data management infrastructure (REDCap Research Electronic Data Capture, version 10.0.23, Vanderbilt University). Trained investigators perform the data entry.

### Sample size

The sample size of this study is calculated to be able to show a 5% difference in participation rate between the two screening strategies, with assumptions based on previous data [7], including an overall participation rate for the home-based screening of 50%, 8% of the participants having elevated ACR, of which 90% will be confirmed by the confirmatory tests, and a participation rate in the elaborate screening of 90%. Adopting a power of 80% and a 2-sided alpha of 0.05, a minimum of 15.032 individuals are to be invited to participate to detect this 5% difference in participation rate between the two screening strategies. This number of individuals also allows discerning a significant difference between both screening strategies in the number of individuals with elevated albuminuria diagnosed with at least one newly discovered CKD or CVD risk factor.

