**Methods:**

This investigator initiated, randomized population-based study will include 15.000 individuals aged 45–80 years, who will be randomly assigned to be invited for a home-based screening test for albuminuria with a more conventional urine collection device or an innovative smartphone application. If the test result is positive upon confirmation (i.e., elevated albuminuria), participants are invited to a central screening facility for an elaborate screening for CKD and CVD risk factors. Participants are referred to their GP for appropriate treatment, if abnormalities are found. Primary endpoints are the participation rate, yield, and cost-effectiveness of the home-based screening and elaborate screening.

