### Study design and procedures

#### Study preparation, randomization, and recruitment

An overview of the study design is shown in Figs 1 and 2. Individuals are randomized in a 1:1 ratio to be invited for home-based screening for albuminuria with either a more conventional urine collection device (UCD) or a smartphone application (App). Randomization is performed by an independent clinical research organization that is unaware of the characteristics of the individuals that are assigned one of the two methods for home-based screening for albuminuria. A 4-block randomization method is used, with randomization performed in batches of 5,000 individuals. Individuals living in one household are randomized to the same group. A unique participant identification code is assigned to all participants. Due to the nature of the study and used study materials, blinding of the participants for the assigned screening method is not feasible.

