### Outcomes

#### Primary outcomes

The primary outcomes are the participation rate and yield of the home-based screening, the elaborate screening, and the overall screening program (Fig 1). The outcomes will be assessed separately for each of the two home-based screening strategies. The participation rate is defined as the number of individuals completing the home-based screening, elaborate screening, and overall screening program relative to the number of invited individuals (with completion including the required confirmation tests). The yield of the home-based screening is defined as the number of individuals who test positive for albuminuria (at least two tests positive) relative to the number of participating individuals. The yield of the elaborate screening is determined as the number of participants with increased albuminuria and newly diagnosed or poorly controlled CVD or CKD risk factors (including hypertension, hypercholesterolemia, type 2 diabetes, and impaired kidney function.

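### The stated minimum of 15.032 invitees does not follow from the participation comparison it is attributed to, so the N, difference, power and endpoint in the sample size paragraph need to be made consistent

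*Protocol article*

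**What the plan says.** The Sample size section names one target: "The sample size of this study is calculated to be able to show a 5% difference in participation rate between the two screening strategies". Its assumptions include "an overall participation rate for the home-based screening of 50" per cent, 8% of participants with an elevated ACR, 90% of those confirmed, and 90% attendance at the elaborate screening. It continues "Adopting a power of 80% and a 2-sided alpha of 0.05" and concludes that "a minimum of 15.032 individuals are to be invited to participate to detect this 5% difference in participation rate between the two screening strategies". A closing sentence adds that the same number suffices to find a significant difference in the number of people with elevated albuminuria and at least one newly found risk factor. It gives neither an effect size nor a power for that comparison.

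The rest of the article fixes the other elements of the calculation:
- **Allocation.** "Individuals are randomized in a 1:1 ratio to be invited for home-based screening", with members of one household placed in the same group (Study preparation, randomization, and recruitment).
- **Denominator.** Participation is counted per invited individual (Primary outcomes).
- **Test.** The two strategies are compared by chi-square test (Statistical analyses).

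**The concern.** The paragraph prints every input of a standard two-proportion calculation and attributes its result to that calculation. The result is nearly five times what the inputs give, so the printed difference, base rate, power, alpha and N cannot all be true together.

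Participation is a primary outcome, and the Discussion expects the trial to support a choice between the two methods. A reader told that the study has 80% power for 5 points will misjudge what it can detect. It has that power for a difference less than half as large. The comparison that may really have needed about 15,000 invitees is left without a stated effect size or power, so its adequacy cannot be judged from this paragraph.

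**Working it through.** **Inputs.** From Sample size: p about 0.50, difference 5%, power 80%, two-sided alpha 0.05, N = 15,032. From the design sections: 1:1 allocation (7,516 per arm), invited individuals as denominator, chi-square test. The normal quantiles are 1.960 and 0.8416.

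**Formula, per arm.** n = [1.960·√(2·p̄(1−p̄)) + 0.8416·√(p1(1−p1) + p2(1−p2))]² / (p1−p2)²

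**Attempt to reproduce 15,032 with 5 percentage points**
- 50% vs 55% (or 45% vs 50%): (1.960·0.7062 + 0.8416·0.7053)² / 0.05² = 1,564.7, so 1,565 per arm and 3,130 in total.
- 47.5% vs 52.5%: 1,568.6, so 1,569 per arm and 3,138 in total.
- With continuity correction: 3,210 to 3,218 in total.
- 15,032 / 3,130 = 4.8.

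**Attempt with 5% read as relative (2.5 points)**
- 50% vs 52.5%: 6,274.0003, rounded up to 6,275 per arm and 12,550 in total. 48.75% vs 51.25%: 12,556.
- With continuity correction: about 12,710. The printed N is still roughly 18 to 20% larger.

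**Other readings, 5 points unless stated**

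| Reading | Total invited |
|---|---|
| 90% power | 4,190 to 4,200 |
| 95% power | 5,180 to 5,192 |
| Divided by 50% participation (not warranted, since the denominator is the invited) | 6,260 to 6,276 |
| Household design effect of 2 (everyone in pairs, perfect correlation) | 6,260 |
| 5 points in elaborate-screening attendance, 90% vs 95%: 2·435 / (0.5·0.08·0.9) | about 24,200 |
| Same, 85% vs 90%: 2·686 / (0.5·0.08·0.9) | about 38,100 |

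None gives 15,032. A relative 5% with a further 20% inflation gives 2·6,275·1.2 = 15,060, which is close, but the article states no such inflation.

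**What 15,032 invited (7,516 per arm) provides**
- Power for 5 points: above 99.99%.
- Power for 2.5 points: about 86.6%.
- Difference detectable with 80% power: (1.960 + 0.8416)·√(0.5/7,516) = 0.0229, about 2.3 points.
- With an assumed household design effect of 1.1 or 1.2 (the article gives none), multiply by √1.1 or √1.2: 2.4 or 2.5 points.

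**Where the cascade leads.** 15,032 × 0.5 × 0.08 × 0.9 × 0.9 = 487 expected attendees at the elaborate screening. In reverse, 487 / (0.9·0.9·0.08) = 7,515.4, which rounds up to 7,516, and 7,516 / 0.5 = 15,032.

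**The case against.** The strongest reply is that the paragraph is condensed or mislabelled rather than miscalculated. It lists the whole cascade, and 487 elaborate-screening attendees traced back through the four rates lands exactly on 15,032. On that view N was set by the yield or elaborate-screening stage and was then credited to participation. This is plausible and limits the conclusion: the article does not show which element is wrong. It is not proof, because the article never prints 487, an agreement this close could be chance, and 5-point differences in elaborate-screening attendance do not reproduce N either.

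A second reply is that 5% may be relative and that the full protocol may hold an inflation factor. The absolute reading is indeed not stated. But the relative reading alone also fails to give 15,032. An article may leave the derivation to the full document, but the figures that it does print should agree with one another.

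A third reply is that nothing is harmed, because the discrepancy is towards too many people. That stands as to power: even with a design effect of 2, power for 5 points is about 99%.

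Three stronger inferences should be resisted:
- **That only about 3,130 people should be invited.** The yield comparison rests on a far smaller group and may need the full number.
- **That the abstract's figure ("will include 15.000 individuals aged") contradicts the stated minimum.** It is 0.2% lower and reads as rounding.
- **That a participation result must be judged against 5 points.** The article uses 5% as a design difference and never calls it a margin of relevance. Such a rule would be new.

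**Conclusion.** The point holds as an inconsistency in the stated basis of the sample size. For home-based participation around 50%, with two-sided alpha 0.05 and 80% power, the number needed is 3,130 to 3,138 for 5 points and about 12,550 for 2.5 points. The stated 15,032 is about 4.8 and 1.2 times these.

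The 80% power and 5-point difference are therefore not the properties of this design. About 15,000 invitees give near-certain detection of 5 points, and 80% power for about 2.3 points before any allowance for household clustering. The 2.4 to 2.5 point range rests on an assumed design effect of 1.1 to 1.2.

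The documents do not support saying that the trial is underpowered for participation, that it should be smaller, or which printed element is the mistaken one.

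**What to change.** Rewrite the Sample size paragraph so that N, difference, power and endpoint belong to one calculation:
1. State whether the 5% difference is absolute or relative, and disclose any inflation that was applied.
2. Give the actual properties of about 15,000 invited: power above 99.99% for 5 points, about 86.6% for 2.5 points, and 80% for about 2.3 points. State any household design effect assumed.
3. Name the endpoint that set N, with its effect size and power. If it was the yield or elaborate-screening stage, show how the 8%, 90% and 90% rates enter and give the expected number of attendees (about 487 by the article's own rates).

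The cost is a text correction by someone with access to the underlying calculation. Recruitment, endpoints and the planned chi-square comparison need not change.

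### The assurance that 15,032 invitations also suffice for the yield comparison is not supported by the stated assumptions: a 5-point participation gap alone gives about 15–20% power

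*Protocol article*

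**What the plan says.** The Sample size section states that the number was "calculated to be able to show a 5% difference in participation rate between the two screening strategies". Its planning values start from "an overall participation rate for the home-based screening of 50" per cent. Among those who take the home test it assumes "8% of the participants having elevated ACR, of which 90% will be confirmed by the confirmatory tests". For attendance at the second stage it takes "a participation rate in the elaborate screening of 90" per cent. Each value is given once, with no split by arm. The result is: "Adopting a power of 80% and a 2-sided alpha of 0.05, a minimum of 15.032 individuals are to be invited to participate".

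The closing sentence extends this to yield: "This number of individuals also allows discerning a significant difference between both screening strategies in the number of individuals with elevated albuminuria" and at least one newly discovered risk factor. No effect size or power accompanies it.

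Under Primary outcomes, yield is primary alongside participation. For the second stage the definition reads: "The yield of the elaborate screening is determined as the number of participants with increased albuminuria and newly diagnosed or poorly controlled"; the text then lists the cardiovascular and kidney risk factors that count. The Statistical analyses section compares yield between strategies with a chi-square test and presents it for the intention-to-screen and per-protocol populations. Allocation is equal: "Individuals are randomized in a 1:1 ratio to be invited for home-based screening".

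**The concern.** The yield sentence follows directly from a calculation about participation, and the only between-arm difference in that calculation is 5% in participation. Elevated albuminuria with a new risk factor occurs in only a few per cent of those invited. A participation gap that is easy to detect among thousands of participants shrinks to a gap of about two dozen people at the end of the cascade.

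This matters because yield is a primary outcome and the Discussion names it among the criteria for choosing between the two methods. Someone relying on the sentence could take a non-significant yield result as coming from an adequately powered comparison.

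**Working it through.** **The stated number.** 15,032 / 2 = 7,516 per arm. It does not follow from the participation inputs. With a two-sided alpha of 0.05, 80% power and a 5-point gap, the usual two-proportion formula needs about 1,565 per arm for 50% versus 55% and 1,569 for 47.5% versus 52.5%, or 3,130 to 3,138 in total. That is a separate matter; 7,516 per arm is taken as given below.

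**Inputs from the Sample size section.** Participation 50%, elevated ACR 8%, confirmed 90%, attending the elaborate screening 90%. The 5% is read as 5 percentage points.

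**Assumed input.** f is the share of attenders with at least one new risk factor. It is not a sample-size input. The Introduction reports, for an earlier cohort, 79% with a comorbidity and 89% of those with one undiagnosed, so 0.79 × 0.89 = about 70%. The most favourable value is f = 100%.

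**Yield per invited person** = participation × 0.08 × 0.90 × 0.90 × f = participation × 0.0648 × f. At 50% participation and f = 100% this is 3.24%, or 7,516 × 0.0324 = 244 people per arm.

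**Power** = Φ[(d − 1.96 × SE0) / SE1], where d is the difference, SE0 = √[2p̄(1 − p̄)/n] and SE1 = √[(p1(1 − p1) + p2(1 − p2))/n].

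With participation 52.5% versus 47.5% and all later rates equal:

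- f = 100%: 3.402% versus 3.078% (256 versus 231 people). d = 0.00324 and SE0 ≈ SE1 ≈ 0.00289, so Φ[(0.00324 − 0.00566)/0.00289] = Φ(−0.84) = 20%.
- f = 70%: 2.392% versus 2.164% (180 versus 163 people). d = 0.00228 and SE0 ≈ SE1 ≈ 0.00243, so Φ[(0.00228 − 0.00477)/0.00243] = Φ(−1.02) = 15%.

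Placing the 5 points at 50/55 or 45/50 instead gives 19–21% and 15–16%. For 80% power in the centred case, about 46,900 per arm would be needed at f = 100% and about 67,300 at f = 70%.

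**Per participant.** The common 8%, 90% and 90% rates imply no difference between arms, so the test would reject about 5% of the time.

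**Detectable difference at 80% power, 7,516 per arm:**

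| Base | f = 100% | f = 70% |
|---|---|---|
| Lower arm at the planned rate | 3.24% vs 4.10% (27% higher) | 2.28% vs 3.01% (32% higher) |
| Gap centred on the planned rate | 213 vs 274 people (29% higher) | 146 vs 197 people (35% higher) |

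A 5-point participation gap gives only 52.5/47.5 = 1.105, about 10% higher. Through participation alone, the centred gap would have to be 0.0081/0.0648 = 12.5 points (f = 100%) to about 15 points (f = 70%).

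Allocation by household was not modelled; clustering would tend to lower power further.

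**The case against.** The strongest reply is that the article never says participation is the only difference between arms. The 8%, 90% and 90% may be overall planning values, and the article gives reasons for yield to differ. One method is a quantitative laboratory assay; the other is a dipstick with 92.9% specificity against a strip analyzer; and the Discussion concedes that the two cut-offs are not identical.

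As an illustration, suppose the App's 7.1% false-positive rate applied independently at each test. Confirmed false positives would be 0.071 × (0.071 + 0.929 × 0.071) × 0.928 = 0.9% of participants, against 7.2% true positives. If the App also had the higher participation, power would be about 71% at f = 100% and 55% at f = 70%. With the accuracy difference alone it stays below 30%, and if the two effects oppose each other they nearly cancel. So 15–20% is one scenario, but none of these reaches 80%.

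Three further points have weight:

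- The 70% share is background data, and it could be higher under the broader primary-outcome definition. The 20% ceiling at f = 100% does not depend on it.
- A 25% relative difference in confirmed positives per invited person (3.6% versus 4.5%) needs about 15,060 in total, close to 15,032. A yield-based calculation may therefore exist in the full protocol. The article does not state one, and that quantity is a different endpoint from the one in the sentence.
- A condensed article may leave an effect size to the full protocol. The point here is not the omission but a positive claim that the printed inputs do not bear out.

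**Conclusion.** The concern stands in conditional form. The stated assumptions do not support the claim about yield. If 5 points of participation is the only difference between arms, power is about 20% at best and about 15% with f near 70%. For 80% power the higher arm must exceed the lower by about 27–35%, depending on f and on where the gap is placed.

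A reader might infer that the sentence is simply false, or that 15–20% is the trial's power for yield. The documents do not support either reading. They state no yield difference, and a large one, for example from unequal test accuracy, would be detectable. Nor does the article plan any equivalence conclusion; that risk lies in how a non-significant result might be read.

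There is also a mismatch of endpoint. The Sample size section counts newly discovered risk factors only, whereas the primary outcome also counts poorly controlled ones.

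**What to change.** Replace the closing sentence of the Sample size section with a quantified statement, for example: with about 7,500 invited per arm, the comparison of the proportion of invited people with elevated albuminuria and a newly diagnosed or poorly controlled risk factor has 80% power for a difference of about 27–35% relative to the lower arm, depending on the share of attenders with such a risk factor and on the base rate; if the arms differ only by 5 points in participation, power is about 15–20%.

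If a larger yield difference was in fact assumed, state it and its basis instead. Use the Primary outcomes wording for the endpoint and recheck the assumed share under that definition. Report yield differences with 95% confidence intervals, and do not infer equivalence from a non-significant test.

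The cost is text only; design, procedures and sample size are unaffected. The claim becomes more modest.

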### Statistical analyses

The statistical package IBM SPSS (version 23, Armonk, NY) will be used for the analysis of the data. Baseline characteristics for continuous variables will be expressed as mean and standard deviation for continuous variables in case of normal distribution, and as median and interquartile range in case of non-normal distribution. Discrete variables will be reported as number and proportions. The primary outcomes, participation rate and yield of screening, will be compared between the two treatment strategies using the Chi-square test. Participation and completion rates will be presented for the intention-to-screen population. Yield of screening will be presented for the intention-to-screen population as well as the per-protocol population. Characteristics of participants and non-responders will be compared using univariable and multivariable logistic regression models. Cost-effectiveness will be assessed using an individual-level health state transition model (microsimulation), comparing the two screening strategies with usual care (no screening). It will be carried out from a Dutch healthcare perspective and the model will be run over the remaining lifetime. Data from literature will be used to estimate participants quality of life, costs of interventions after the elaborate screening, the efficacy of interventions to prevent CVD and CKD progression, and the costs associated with CVD and CKD events. Effectiveness will be calculated expressed in total costs and total effects (in QALYs) per screening method. Incremental effects will be calculated and the incremental cost-effectiveness ratio (ICER), will be determined, defined as incremental costs divided by incremental gain in QALYs.

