## Materials and methods

### Study setting and population

The THOMAS study is designed as an investigator-initiated, prospective, randomized population-based screening study. The University Medical Center Groningen, the Netherlands, acts as the coordinating center. Individuals from the general population are eligible if they are aged 45–80 years and living in the region of Breda, the Netherlands. Individuals are excluded when institutionalized. A random sample of men and women aged 45–80 years living in the region of Breda is drawn by Statistics Netherlands. This sample represents the Dutch population with respect to distribution of age, sex and socioeconomic class (as assessed by postal code area) [16]. The Dutch Ministry of the Interior and Kingdom Relations provides names, dates of birth, sex, and addresses.

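### The participation comparison uses an unadjusted Chi-square test although age and sex are supplied for the invited sample: a small, optional gain in precision is left unused

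*Protocol article*

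**What the plan says.** The Protocol article, Statistical analyses, fixes the method for both primary outcomes: "The primary outcomes, participation rate and yield of screening, will be compared between the two treatment strategies using the Chi-square test". No covariate enters that comparison. The same section plans multivariable logistic models, but only to contrast the characteristics of participants with those of non-responders.

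Study setting and population describes what is held before invitation: "The Dutch Ministry of the Interior and Kingdom Relations provides names, dates of birth, sex, and addresses". Socioeconomic class appears there only at area level: "This sample represents the Dutch population with respect to distribution of age, sex and socioeconomic class (as assessed by postal code area").

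Study preparation, randomization, and recruitment describes 1:1 allocation in blocks of four, run in batches of 5,000, with members of one household placed in the same arm. It mentions no stratification by age, sex or class.

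Sample size aims "to show a 5% difference in participation rate between the two screening strategies" and assumes "an overall participation rate for the home-based screening of 50" per cent. It also assumes "8% of the participants having elevated ACR, of which 90% will be confirmed by the confirmatory tests".

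Primary outcomes defines participation relative to those invited, and home-based yield relative to those who participate. Statistical analyses adds that yield will also be shown for the intention-to-screen population.

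**The concern.** Age, sex and area class are fixed before randomization, cannot be affected by the assigned test, and are available for responders and non-responders alike. It is plausible that they predict participation: one arm requires a smartphone application, and the Discussion calls CKD prevalence age-dependent. Where baseline variables predict an outcome, standardizing the arm difference over them removes some residual variance and the effect of chance imbalance, and leaves the randomized comparison intact.

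At stake is the width of the interval around the participation difference, which the Discussion intends to use in choosing the more promising method. The question is how much width could be saved, and for which outcomes.

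**Working it through.** **Inputs from the Protocol article.** 15,032 invited, 1:1, so 7,516 per arm; 50% participation; 8% of participants positive, of whom 90% are confirmed.

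**Assumption.** R², the share of outcome variance explained by the covariates, is not in the article. I use 1% to 6%.

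**The plan's own figure.** "Adopting a power of 80% and a 2-sided alpha of 0.05, a minimum of 15.032 individuals are to be invited to participate". I could not reproduce it. With the usual two-proportion formula, an absolute 5-point difference near 50% needs 3,130 to 3,138 people in total. A relative 5% (2.5 points) needs 12,550 to 12,556. That is a separate matter; below I take 15,032 as given.

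**Unadjusted standard error, participation.** √(2 × 0.5 × 0.5 / 7,516) = 0.00816, or 0.816 points.

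**What R² could be.** If participation changes linearly by g across a uniform covariate, the variance explained is g²/12. For two independent covariates with the same gradient, R² = 2(g²/12)/0.25.
- R² = 1% corresponds to g = √(6 × 0.25 × 0.01) = 0.12, about 12 points.
- g = 0.20 gives 2 × 0.00333/0.25 = 2.7%.
- g = 0.30 gives 2 × 0.0075/0.25 = 6%.

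**Adjusted standard error** = 0.816 × √(1 − R²). **Equivalent extra invitees** = 15,032 × (1/(1 − R²) − 1).

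| R² | SE (points) | Equivalent extra invitees |
|---|---|---|
| 0 | 0.816 | 0 |
| 1% | 0.812 | 152 |
| 2.7% | 0.805 | 417 |
| 6% | 0.791 | 959 |

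**Interval width.** The 95% half-width goes from 1.96 × 0.816 = 1.60 points to 1.96 × 0.791 = 1.55 at best, a saving of 0.05 points.

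**Power.** For 47.5% versus 52.5%, power is 99.9985% unadjusted. For a 2.5-point difference it is 86.6% unadjusted, 86.9% at R² = 1% and 88.2% at R² = 5%.

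**Intention-to-screen yield** (read as confirmed positives among all invited). The expected proportion is 0.50 × 0.08 × 0.90 = 3.6%, and the SE is √(2 × 0.036 × 0.964 / 7,516) = 0.304 points. Assume a threefold age gradient, from 1.8% to 5.4%. Then R² = (0.036²/12)/(0.036 × 0.964) = 0.3%, and the SE becomes 0.304 × √0.997 = 0.303 points. The gain is practically nil.

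**Household allocation.** The figures above treat people as independent. The article does not say how many invited people share a household, so the design effect is unknown. A design effect of 1/(1 − 0.06) = 1.06 would cancel the whole gain at R² = 6%. Under assumed design effects of 1.2 to 2.0, unadjusted power for 2.5 points falls to 79.9% and 58.2%.

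**The case against.** The strongest objection is that nothing here is wrong. A Chi-square test in a 1:1 randomized comparison is valid without covariates. A reader might infer that the plan omits a stratification factor, but the article describes no stratification by age, sex or class. A reader might also infer that the study loses needed power. On the absolute reading of the 5% target power is already above 99.99%, and on the relative reading the gain is 0.3 to 1.6 points for R² of 1% to 5%. Chance imbalance is small too: at R² = 6% the component removed has a standard deviation of 0.816 × √0.06 = 0.2 points. All of this stands. Adjusted models and effect-size reporting may also be in an analysis plan that is not shown, so their absence from the article is not itself a fault.

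A further tempting reading is that adjustment gives free precision for every primary outcome. The documents do not support it. Home-based yield as defined in Primary outcomes is conditional on participating, which happens after randomization and may differ by arm. Adjusting for age and sex does not restore the randomized comparison there, and moving that outcome to all invited people would change what it measures.

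Nor are the covariates entirely free. The article does not say that they are complete. Postal-code class is used to describe the sample, not stated to be a recorded variable, and Data management keeps names and addresses on a separate platform from the pseudonymized results. Class would have to be derived and linked.

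What survives is narrow: age and sex are supplied for the sample, the stated test ignores them, and using them costs little.

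**Conclusion.** The point holds as a small, optional improvement to the participation comparison. Under an assumed R² of 1% to 6%, the standard error falls from 0.816 to between 0.812 and 0.791 points, a reduction of 0.5% to 3%. The size depends wholly on R², for which the article gives no figure. For intention-to-screen yield the gain is negligible, and the reason to report it in the same way is consistency. For yield per participant neither added precision nor protection by randomization should be claimed.

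Covariates do not address the shared allocation of households, which the plain Chi-square test also ignores and which may matter more than the precision gained. An adjusted model that ignored households would leave that weakness in place.

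**What to change.** In the Protocol article, Statistical analyses, or in the analysis plan if it covers this comparison, settle the following before the arms are compared:

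- Report the absolute difference between arms in participation, and in intention-to-screen yield, each with a 95% confidence interval. Standardize it over all invited people from a logistic model with arm, age and sex.
- Add postal-code socioeconomic class where it can be derived and linked.
- Use household-robust standard errors, since household members share an arm.
- Keep the unadjusted Chi-square result as supportive.
- Leave the per-participant definition of yield in Primary outcomes as it is. Report it alongside, and state that its denominator forms after randomization.

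The cost is a change of wording and a little programming, plus a household identifier in the analysis file and, if class is used, a linkage step. No new data collection or extra invitations are needed.
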